## DISCUSSION

3

The initiative of ICASMAP study utilizes MR vessel wall imaging to determine the etiology of ICAS and the rate of progression of ICAD during 2‐year follow‐up. This study may unveil the spectrum of diseases, including atherosclerosis, dissection, arteritis, moyamoya disease, and RCVS, that lead to ICAS in Chinese symptomatic patients. This study may also provide a clue to the ICAD progression associated risk factors which will be helpful for improving treatment strategies in clinical settings.

The spectrum of intracranial artery diseases that lead to ICAS has been studied in Asian young populations and targeted the middle cerebral artery. Ahn et al. (2015) studied 95 South Korean young patients (≤55 years old) with one or none atherosclerosis risk factor and unilateral severe stenosis in middle cerebral artery (stenosis > 50%) using high‐resolution MR vessel wall imaging. Investigators found that the most prevalent disease was moyamoya disease (30.5%), followed by atherosclerosis (27.4%), dissection (23.2%), and vasculitis (18.9%) in young adult patients with none or one atherosclerotic risk factor (Ahn et al., 2015). In contrast, Xu et al. (2017) recruited 122 Chinese young patients (from 18 to 45 years old) with unilateral middle cerebral artery stenosis to determine the etiology of ICAS using high‐resolution MR vessel wall imaging and found the most common etiology of ICAS was atherosclerosis (80.3%). The difference in prevalence of atherosclerotic disease between studies by Ahn et al. and Xu et al. may be due to the different definition of atherosclerosis and different profiles of study populations. The atherosclerosis was defined as eccentric wall lesion in Xu's study, whereas the lesion with eccentric and irregular wall thickening was defined as atherosclerotic disease in study by Ahn et al. The ICASMAP study will recruit symptomatic patients with wide range of age (from 18 to 80 years old) and larger sample size which may broaden the spectrum of etiology of ICAS in stroke patients.

MR vessel wall imaging has been widely used to differentiate the pathology of ICAS according to the imaging features of location, shape, signal pattern, remodeling, and contrast enhancement (Choi et al., 2015; Mossa‐Basha et al., 2015). Primarily, for assessing intracranial artery diseases, investigators utilized two‐dimensional (2D) imaging sequences which have the following disadvantages: (a) smaller coverage; (b) lower inter‐plane resolution; (c) insufficient blood suppression; and (d) long scan time. To overcome these technical limitations, three‐dimensional (3D) imaging techniques have been proposed and optimized for intracranial vessel wall imaging, particularly spin echo‐based sequence of VISTA (Qiao et al., 2011; Wang et al., 2016; Yang et al., 2016) or SPACE (Fan et al., 2017; Yang et al., 2017; Zhang et al., 2015). These 3D imaging sequences enable whole brain vessel wall imaging by providing large longitudinal coverage, isotropic spatial resolution, and excellent blood flow suppression. A recent consensus on intracranial MR vessel wall imaging recommended that T1‐weighted (or proton‐density‐weighted) vessel wall sequences before and after intravenous administration of gadolinium can be used to differentiate the etiology of ICAS (Mandell et al., 2017). In the ICASMAP study, pre‐ and post‐contrast enhanced 3D T1‐VISTA/SPACE sequences will be acquired to evaluate the intracranial artery wall in most of intracranial vascular beds. This study may provide more comprehensive view for lesion distribution in intracranial arteries.

The role of baseline intracranial artery plaque features in progression of ICAD remains unclear. Previous studies on relationship between baseline atherosclerosis and its progression are based on angiographic approaches. Mizukami, Shimizu, Maki, Shiraishi, and Hasegawa (2015) found that the global stenosis score, which is calculated by measuring the extent of middle cerebral arteries and the basilar artery, and the degree of carotid stenosis were significantly associated with progression of ICAS. Ryu et al. (2014) studied 102 subjects with ICAS and found that symptomatic ICAS subjects had greater risk of stenosis progression than asymptomatic ones. In carotid arteries, a number of studies have shown that presence of intraplaque hemorrhage (Sun et al., 2012; Takaya et al., 2005), maximum wall thickness (Xu et al., 2014), maximum lipid‐rich necrotic core percentage (Xu et al., 2014), and negative remodeling (Bianda et al., 2012) determined by MR vessel wall imaging are effective predictors for carotid plaque progression. However, there is no MR vessel wall imaging‐based evidence to show these relationships in ICAD. The ICASMAP study will provide a clue to the intracranial atherosclerotic plaque characteristics on MR vessel wall imaging at baseline that influence plaque progression.

It has been evidenced that some clinical risk factors and blood biomarkers were significantly associated with the progression of ICAD determined by angiography. A study by Miyazawa et al. (2007) showed that diabetes (OR, 6.771; *p* = 0.0004) and smoking (OR, 7.574; *p* = 0.0019) were correlated with the progression of ICAS. Shimizu et al. (2013) found that interleukin‐6 (HR, 1.215; 95% CI 1.002‐1.473) was a risk factor for the progression of ICAD in stroke patients. Another study by Arenillas et al. (2008) recruited 75 symptomatic ICAD patients and found that C‐reactive protein (CRP > 5.5 mg/L; HR, 5.4; 95% CI, 2.3–12.7; *p* = 0.0001) and plasminogen activator inhibitor‐1 (PAI‐1 > 23.1 ng/ml; HR, 2.4; 95% CI, 1.0–5.8; *p* = 0.05) were related to the progression of ICAD. In the clinical treatment aspect, investigators demonstrated that statin therapy may inhibit the progression of symptomatic ICAS in middle cerebral or/and basilar arteries (Kim et al., 2012). In addition, Kwon et al. (2005) provided evidence that cilostazol may prevent the progression of symptomatic ICAS. Since above studies are based on stenosis progression measured by angiographic approaches, the influence factors of plaque progression determined by MR vessel wall imaging remain unknown. The ICASMAP study will link potential influence factors to intracranial artery plaque progression assessed by MR vessel wall imaging and may help to improve the management of ICAD patients.

### Limitations

3.1

Our study has several limitations. First, in this study, we recruited patients from Beijing–Tianjin–Hebei regions of China who represent urban residents. It will be interesting to assess the etiology of ICAS and progression of ICAD in rural regions in China in future studies. Second, this study focused on the patients who had 30%–99% stenosis. The etiology of intracranial artery with lower grade stenosis (<30% stenosis) is not studied. Third, this is MR vessel wall imaging study using different MR platforms (Philips and Siemens). The variability between Philips and Siemens MR scanner in measuring intracranial plaque features is unclear. Future studies focusing on the reproducibility among different MR platforms are warranted.

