### Study design and population

2.1

The ICASMAP study (NCT03417063) is a prospective, observational, and multicenter study. This study planned to recruit 300 patients (age range: 18–80 years old) who had recent ischemic stroke or transient ischemic attack (TIA; within 2 weeks after onset of symptoms) and ICAS (stenosis range from 30% to 99% that is the responsible lesion for symptoms) in at least one vascular bed determined by computed tomography angiography (CTA) or MR angiography. The ICAS lesions can be located in intracranial internal carotid artery, basilar artery, intracranial segment of vertebral artery (V4), M1 segment of middle cerebral artery, A1 segment of anterior cerebral artery, or P1 segment of posterior cerebral artery. The patients will be recruited from 18 different hospitals across Beijing–Tianjin–Hebei region in China. The exclusion criteria include the following: (a) severe carotid artery atherosclerotic disease (stenosis ≥ 70%); (b) cardiogenic thrombosis; (c) heart failure or respiratory failure; (d) renal dysfunction (serum creatinine ˃133 μmol/L); (e) serious disturbance of consciousness; (f) cerebral neoplasms; (g) intracranial hemorrhage; (h) claustrophobia; (i) contraindications to MRI; and (j) pregnant or plan to pregnant within recent 2 years. All subjects will undergo brain and intracranial artery MR imaging. For subjects who were diagnosed with ICAD (*n* > 200), the clinical follow‐up will be conducted at 3, 6, 12, and 24 months and the MR imaging follow‐up will be performed at 12 and 24 months, respectively. Previous studies reported that the progression rate of ICAS was 3.86% per year (Ryu et al., 2014) and the intra‐reader and inter‐scan variation in measuring maximum wall thickness of intracranial plaques was 6.67% (Zhang et al., 2018). Therefore, it might be reasonable to detect the 2 years’ progression of intracranial atherosclerosis disease (7.72%) which is greater than the variation of quantitative measurement by MRI. A flow chart of the study procedures is presented in Figure 1. The study protocol was approved by local Institutional Review Board, and all patients provide written informed consent.

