### MR imaging

2.4

Baseline MR examination includes brain MR imaging and intracranial artery high‐resolution MR vessel wall imaging. All MR examinations will be performed on 3.0T Philips or Siemens MR scanners with 8‐channel phase‐array head coil or 16‐channel neurovascular coil. Brain MR imaging was conducted using a standard protocol including T1‐weighted (T1W), T2‐weighted (T2W), T2‐fluid‐attenuated inversion recovery (FLAIR), T2*‐weighted (T2*W), and diffusion‐weighted image (DWI) sequences. The imaging parameters are detailed in Table 1. The intracranial artery MR vessel wall imaging protocol includes three‐dimensional (3D) time‐of‐flight (TOF) MR angiography and pre‐ and post‐contrast T1 volumetric isotropic turbo spin echo acquisition (VISTA) at Philips MR platform or T1 sampling perfection with application‐optimized contrast using different flip angle evolutions (SPACE) sequence at Siemens MR platform. The 3D TOF imaging sequence was acquired with the following parameters: turbo field echo/fast low angle shot sequence, repetition time 25/21 ms, echo time 3.5/3.6 ms, field of view 180 × 180/173 × 199 mm³, matrix 300 × 300/384 × 301, and thickness 0.6 mm. The VISTA/SPACE imaging sequence was acquired using the following parameters: fast spin echo sequence, repetition time 800/900 ms, echo time 19/24 ms, field of view 200 × 181 × 45/158 × 158 × 158 mm³, matrix 332 × 300 × 150/256 × 256 × 246, and thickness 0.6 mm. The intracranial artery MR imaging parameters are presented in Table 2. The post‐contrast MR vessel wall imaging will be performed at baseline by intravenous administration of gadolinium contrast agent (Magnevist, Bayer Schering Pharma AG, Berlin, Germany) with the dose of 0.1 mmol/Kg. The recruited patients who were diagnosed with atherosclerosis in intracranial arteries by baseline MR vessel wall imaging will be eligible for 2‐year follow‐up study using MR imaging. The MR vessel wall imaging in the follow‐up study will be performed at the same MR platform to the baseline at 12 and 24 months by acquiring pre‐contrast T1‐VISTA or T1‐SPACE imaging sequence with the same imaging parameters to the baseline.

**Table 1 brb31154-tbl-0001:** Brain MR imaging parameters

	T1W	T2W	T2‐FLAIR	DWI
Sequence	FFE^a^/FISP^b^	TSE	TSE	EPI
TR, ms	233	3,000	7,000	2,858
TE, ms	4.6	80	140	92
FOV, mm³	230 × 183 × 133	230 × 183 × 133	230 × 230 × 133	230 × 230 × 133
Matrix	400 × 255	400 × 255	256 × 195	128 × 126
Thickness, mm	5.5	5.5	5.5	5.5

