Scan time	1′58″	1′48″	1′52″	34″

FFE, fast field echo; FISP, fast imaging with steady‐state precession; TSE, turbo spin echo; EPI, echo planar imaging; TR, repetition time; TE, echo time; FOV, field of view.

^a^The imaging sequence is from Philips MR platform.^b^The imaging sequence is from Siemens MR platform; All the imaging orientations are transverse.

**Table 2 brb31154-tbl-0002:** Intracranial artery MR vessel wall imaging parameters

	3D TOF	T1‐VISTA^a^/SPACE^b^
Sequence	TFE^a^/FLASH^b^	TSE
TR, ms	25/21	800/900
TE, ms	3.5/3.6	19/24
Echo train length	‐	30/27
FOV, mm³	180 × 180/173 × 199	200 × 181 × 45/158 × 158 × 158
Matrix	300 × 300/384 × 301	332 × 300 × 150/256 × 256 × 246
Thickness, mm	0.6	0.6
Scan time	5′39″/6′	7′01″/8′06″
Orientation	Axial	Axial/Coronal

3D TOF, three‐dimensional time‐of‐flight; FOV, field of view; FLASH, fast low angle shot; FSE, fast spin echo; T1‐VISTA, T1 volumetric isotropic turbo spin echo acquisition; T1‐SPACE, T1 sampling perfection with application‐optimized contrast using different flip angle evolutions; TE, echo time; TFE, turbo field echo; TR, repetition time.

^a^The imaging sequence is from Philips MR platform.^b^The imaging sequence is from Siemens MR platform.

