### End points

2.6

The presence of progression of intracranial artery atherosclerotic plaques is the primary end point. The progression of intracranial plaque is defined when it meets any of the following criteria at 1‐ or 2‐year follow‐up compared with baseline measurements: (a) the maximum wall thickness increased ≥10% compared with baseline; (b) the stenosis increased by one or more grades on TOF MRA or MR vessel wall imaging; (c) occurrence of T1 hyperintensity within plaque; or (d) the enhancement increased by one or more grades on post‐contrast T1 VISTA/SPACE images. Secondary end points include new ischemic stroke or TIA at any vascular territories, or all‐cause death.

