### Statistical analysis plan

2.9

The continuous variables will be presented with mean ± standard deviation, and the categorical variables will be described as percentage. The prevalence of different vascular diseases, such as atherosclerosis, dissection, arteritis, moyamoya disease, and RCVS, that lead to ICAS in different age groups (<40, 40–50, 50–60, 60–70, and >70 years) will be calculated. The morphological measurements, T1 hyperintensity, enhancement patterns, and remodeling will be compared among different arterial diseases using One‐Way ANOVA or Mann–Whitney U test when appropriate. The progression rate of ICAD was calculated. Spearman correlation will be analyzed to determine the association of plaque features at baseline, clinical risk factors and blood biomarkers with progression of ICAD. Logistic regression model will be performed to calculate the odds ratio (OR) and corresponding confidence interval (CI) of plaque features at baseline, clinical risk factors and blood biomarkers in discriminating progression of ICAD before and after adjusting for confounding factors. Cox regression will be analyzed to calculate the hazard ratio and corresponding 95% CI of baseline intracranial artery vessel wall MR features in predicting for the cerebrovascular events. The intraclass correlation coefficient (ICC) and Kappa value were calculated for continuous and categorical variables in intra‐reader and inter‐reader reproducibility studies, respectively. All statistical analyses will be performed using SPSS 16.0 (SPSS Inc., Chicago, IL) and SAS (SAS Inc., North Carolina, NC).

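### Philips–Siemens measurement variability is declared unclear, yet no analysis stated in section 2.9 names MR platform

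*Protocol article*

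**What the plan says.** Section 2.4 (MR imaging) allows two vendors: "All MR examinations will be performed on 3.0T Philips or Siemens MR scanners". The vessel wall sequence differs between them: T1-VISTA on Philips and T1-SPACE on Siemens. In Table 2 the fields of view are "200 × 181 × 45/158 × 158 × 158" mm, repetition times 800/900 ms, echo times 19/24 ms, and orientation axial/coronal.

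Follow-up vessel wall imaging "will be performed at the same MR platform to the baseline at 12 and 24 months by acquiring" the pre-contrast sequence "with the same imaging parameters to the baseline". Section 2.6 (End points) defines progression against the patient's own baseline. One of its four criteria is that "the maximum wall thickness increased ≥10% compared with baseline".

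Section 3.1 (Limitations) states: "The variability between Philips and Siemens MR scanner in measuring intracranial plaque features is unclear". It asks for future work on this and does not refer back to the analysis.

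Section 2.9 (Statistical analysis plan) lists ANOVA or Mann–Whitney comparisons of imaging features among diseases, Spearman correlations with progression, logistic models for progression, and a Cox model of baseline vessel wall features for cerebrovascular events. Only the logistic models are described as adjusted, "before and after adjusting for confounding factors", and those factors are not listed. Platform appears in none of the four.

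**The concern.** The article identifies a source of measurement error and then states analyses that do not address it. Two routes remain open after the same-platform rule.

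- **Baseline features.** Wall thickness, T1 hyperintensity (a 1.5-fold signal threshold) and enhancement grade are single-time-point readings. If the two sequences read them differently, the offset enters the among-disease comparisons directly. It also enters the predictors in the Spearman, logistic and Cox analyses. Own-baseline comparison protects the change score, not these readings.
- **Repeatability.** Criterion (a) is a threshold on a noisy measurement. If one platform is noisier, more of its unchanged lesions will be counted as progressed.

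The two can combine. If one platform both flags a baseline feature more often and produces more false progressors, that feature acquires an association with progression that is not biological, even when the patients on the two platforms are alike. At stake are the progression rate (a primary objective), the risk-factor odds ratios (the secondary objective), and the imaging comparison between diseases.

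**Working it through.** The article gives no figure for a platform difference, so there is none to reproduce. Its one measurement-error figure is 6.67% for maximum wall thickness (section 2.1), described as intra-reader and inter-scan variation. It is not said whether this is a per-scan coefficient of variation (CV) or the SD of a difference, and it is not split by platform.

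**Step 1: what the same-platform rule removes.** Let B and F be the true baseline and follow-up thickness.
- Proportional offset k: kF/kB − 1 = F/B − 1, so it cancels exactly.
- Additive offset, with an assumed 1.50 to 1.65 mm (+10.0%): at −0.1 mm, 1.55/1.40 − 1 = 10.7%; at +0.2 mm, 1.85/1.70 − 1 = 8.8%. The effect is small.

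**Step 2: what it leaves, repeatability.** For an unchanged lesion at one follow-up scan, P(observed rise ≥10%) = 1 − Φ(10/SD of change). If the error figure is a per-scan CV, the SD of change is √2 × CV. The 5% and 8% values are assumptions chosen to bracket 6.67%.

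| Error figure | Read as per-scan CV | Read as SD of change |
|---|---|---|
| 5% | 7.9% | 2.3% |
| 6.67% | 14.5% | 6.7% |
| 8% | 18.8% | 10.6% |

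**Step 3: observed progression by platform.** Let t be true progression, with every true progressor counted. Observed rate = t + (1 − t) × P.
- t = 0.20 (the section 2.7 assumption), per-scan reading: 0.20 + 0.80 × 0.079 = 0.263, against 0.20 + 0.80 × 0.188 = 0.351. OR = (0.351/0.649)/(0.263/0.737) = 1.51.
- t = 0.10, per-scan reading: 0.171 against 0.270, OR 1.79.
- t = 0.20, SD-of-change reading: 0.20 + 0.80 × 0.023 = 0.218, against 0.20 + 0.80 × 0.106 = 0.285. OR about 1.4.
- Equal repeatability on both platforms: OR 1.0.

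These figures cover one criterion at one visit. The end point allows any of four criteria at 12 or 24 months.

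**Step 4: spill-over onto a factor with no true effect.** Assume equal numbers on the two platforms.
- Factor balanced across platforms, or equal observed progression: OR 1.00.
- Factor present in 40%/60%, observed progression 18%/24%: exposed 0.4 × 0.18 + 0.6 × 0.24 = 0.216; unexposed 0.6 × 0.18 + 0.4 × 0.24 = 0.204; OR 1.08.
- Factor present in 30%/70%, observed progression 15%/30%: exposed 0.255, unexposed 0.195, OR 1.41.

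A spurious odds ratio therefore needs both the factor and the observed progression to differ by platform. For a baseline imaging feature, a measurement offset alone can supply the first condition. For a clinical risk factor, patient mix would have to differ by platform.

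**The case against.** The strongest reply is that the design already handles the main route. Each patient stays on one platform with fixed parameters, progression is judged against the patient's own baseline, and images are read in one core lab blinded to clinical information and time point. A reader might infer that a Philips–Siemens difference could itself be counted as progression. Step 1 shows that a constant offset cancels or nearly cancels, so the documents do not support that reading.

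It can also be said that the article never states that platform is ignored. The logistic confounders are unlisted, and a condensed article commonly leaves them to the full plan. This stands for the logistic models. It does not cover the among-disease tests, the Spearman correlations or the Cox model, which are stated with no adjustment.

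The 5% versus 8% split is assumed, and nothing in the article says that repeatability differs by platform. False crossings of a 10% threshold also occur with a single scanner. This stands, and is why the range starts at an odds ratio of 1.0.

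Three further inferences are tempting but unsupported:
- **Platform tracks hospital and case mix.** The article says "The patients will be recruited from 18 different hospitals" but not which hospital uses which scanner.
- **The 45 mm slab misses segments that the 158 mm volume covers.** The orientations differ, no shortfall in the listed segments is shown, and section 2.9 states no segment-by-segment analysis.
- **Platform noise distorts the Cox outcome.** That outcome is clinical events, which measurement noise cannot create. Only the imaging predictors can be affected.

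**Conclusion.** The point holds in a limited form. The article calls between-platform variability in measuring plaque features unclear, and its stated analyses name no platform term. Two things remain exposed after the same-platform rule: baseline imaging features, whether compared between diseases or used as predictors, and the false-progression rate at the 10% threshold if repeatability differs.

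The size is not known. The platform odds ratio for observed progression is 1.0 under equal repeatability and about 1.5 under the assumed 5% versus 8% per-scan errors with 20% true progression. A null factor would show an odds ratio between 1.00 and 1.41 across the scenarios tried. Confounding is possible but not demonstrated, since the article gives no platform split. The section 2.8 reproducibility study does not settle the matter: it describes repeat readings in 15 subjects, with no repeat scans and no platform breakdown. No sample-size figure changes. The change is worth making because it is cheap and the study's own data allow it; the flaw does not invalidate the design.

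**What to change.** In section 2.9:

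- Include MR platform (Philips/Siemens) as a covariate in the logistic progression models, named explicitly among the adjustment factors.
- Use platform as a stratum in the Cox model.
- Adjust the among-disease comparisons of imaging features for platform where numbers allow. With more than 200 of 300 patients expected to have ICAD, fewer than 100 remain across the other diseases, so some cells will be too sparse.
- Report the progression rate by platform beside the overall rate.

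No new scans are needed, because the platform follows from the sequence acquired (VISTA or SPACE). The cost is one degree of freedom in the logistic models and slightly wider intervals. That is affordable with about 200 × 0.85 × 0.20 = 34 or more expected progressors.

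A random intercept over 18 hospitals is not advised: at about 34 progressors it would rest on roughly two per hospital. Nor do the documents support restricting comparisons to segments covered by both acquisitions. A platform term removes an average offset between platforms. It does not correct the overall progression rate for false crossings, which is why the by-platform rates should be shown.
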